### Data monitoring and management

All study data will be captured electronically in a secured online survey platform (Qualtrics B.V., Amsterdam, the Netherlands; www.qualtrics.com). The data will be uploaded into the IBM SPSS database. All data will be kept in separate databases and merged into a master database only after data collection is completed and each individual database is locked. Qualitative data will be collected using audio recordings, written field notes, and memos. The data will be anonymized but linked with the trial identifier. The program Atlas.ti will be used to analyze the qualitative data. Recordings will be stored in a secure, password-protected folder. All data will be anonymized and electronically stored at the VU Amsterdam, separate from identifying information. Access to data will be password-protected. Only the lead investigators and trial researchers will have access to the final dataset. All collected data will be used only for the purposes of this research.

### Harms

The intervention is considered safe, with very low risk of adverse events. We estimate that the benefits of the study will be greater than any possible risk. Serious adverse events (e.g., negative life events, symptoms) are regularly monitored by the coach during the intervention. They will be documented by the research team and reported immediately to the principal investigator. If there is an adverse event, it will be discussed with a senior clinical academic independent of VU University and the research team. Appropriate courses of action will be agreed on and implemented. Participants are also advised to contact their general practitioner if they experience increased mental health symptoms.

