### Procedure

Nonprofessional caregivers will be recruited via the Dutch Depression Association and by advertisements on the Internet and other media (see Figure 1). Caregivers who are interested in taking part can find more information about the study on the website of the Mental Health Fund (Fonds Psychische Gezondheid), which hosts the study website. If they are interested in taking part in the study, they can register via the website. Next, they have to provide digital informed consent before being directed to the online baseline assessment. Those who are eligible to take part will be randomized to the intervention condition or the WLC group. Subjects in the intervention condition will have access to the online intervention for 6 weeks, while those assigned to the WLC condition will get access to the E-care 4 caregivers intervention after the 6-week assessment. Participants in both arms will be invited to complete an online assessment 6 weeks after baseline. Participants in the E-care 4 caregivers intervention group may also be approached for a qualitative interview. The Consolidated Standards of Reporting Trials (CONSORT) will be followed for reporting the trial [17]. Participants who complete all data entry points will receive an incentive of 25 euros.

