### Intervention: E-care 4 caregivers

The online self-management course comprises eight modules. The elements of it are described in Table 1. The modules include theory, exercises, examples of caregivers` experiences, and short videos. This intervention will include personalized feedback provided by a coach and a diary app. An Internet forum that is developed as a closed group on Facebook will also be a part of the online course. This forum is used for peer contact and is moderated by a coach.

**Table 1 Tab1:** Content online intervention

Themes	Topics	Goals
1. What is depression?	Psychoeducation concerning symptoms, diagnosis, types, and causes of, as well as treatment options for, depression	To familiarize caregivers with the nature of the depressive disorder and its treatment to enable recognition of symptoms
2. Implications of depression for the caregiver	Emotions that can arise for the caregiver and the family, grief processes that occur, and practical implications of the depression	To recognize, validate, and accept negative emotions that can arise in a caregiver when facing the situation that a loved one has depression
3. How to think differently	Automatic thoughts, cognitive distortions, and how to correct these using principles of cognitive therapy	Using cognitive principles to recognize dysfunctional thoughts and change them to help caregivers in this stressful situation
4. Signaling stress and burnout	Psychoeducation about causes and signs of stress using the capabilities/workload model	Recognition and/or prevention of symptoms of overburdening and stress
5. Caring for yourself	Tips to better take care of yourself and your own boundaries with exercises about help-seeking, assertiveness, time-management, and relaxation exercises	Preventing and/or decreasing symptoms of overburdening and stress via various exercises
6. Learning to communicate better	Psychoeducation about communicating with someone with depression using the disarm technique and principles of emotionally focused therapy	To recognize your own role in communicating while understanding someone with depression better to avoid constant repetitive arguments
7. Coping with suicidality	Psychoeducation about suicidality, tips to communicate about suicidality, establishing and following safety procedures	Empowering caregiver with more knowledge about suicidality and safety measures as well as gaining more confidence in communication and setting boundaries

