### Assessments

All quantitative assessments are self-report measures and will be administered online. Semistructured qualitative interviews will be conducted by telephone. An overview of the questionnaires and their time of assessment is provided in Table 2.

**Table 2 Tab2:** Overview of questionnaires and the time of assessment

Questionnaire	Baseline	6 weeks
Demographic variables, participant + depressed family member	X	
Kessler Psychological Distress Scale (K10)	X	X
Generalized Anxiety Disorder Scale (GAD7)	X	X
Zarit Burden Interview (ZBI-12)	X	X
Euro-Qol (EQ-5D)	X	X
System Usability Scale (SUS)		X
Pearlin Mastery Scale	X	X

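### The only adverse-event ascertainment described runs through the coach, whom the wait-list arm lacks until after week 6, so events as collected cannot be compared between arms

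*Protocol article*

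**What the plan says.** The Harms section of the protocol article names one way in which events come to light: "Serious adverse events (e.g., negative life events, symptoms) are regularly monitored by the coach during the intervention". The next sentence deals with what happens to those events: "They will be documented by the research team and reported immediately to the principal investigator". The section then provides for discussion with an independent senior clinician and gives all participants one piece of advice: "Participants are also advised to contact their general practitioner if they experience increased mental health symptoms".

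The section on the intervention makes the coach one of its components: "This intervention will include personalized feedback provided by a coach and a diary app". The coach also moderates the peer forum. Under Procedure, "those assigned to the WLC condition will get access to the E-care 4 caregivers intervention after the 6-week assessment".

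The contact that the two arms share after randomization is also under Procedure: "Participants in both arms will be invited to complete an online assessment 6 weeks after baseline". Table 2 (Assessments) lists what is asked: demographic variables at baseline only, the SUS at 6 weeks only, and K10, GAD7, ZBI-12, EQ-5D and the Pearlin Mastery Scale at both times.

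**The concern.** When events are sought actively in one randomized arm and not in the other, the counts differ even if the underlying risk does not. The Harms section's own examples make this worse. Negative life events and symptoms are to be expected as background in caregivers of people with depression, so regular contact will turn some up whether or not the course causes any.

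Two misreadings could follow. An excess of recorded events in the intervention arm could be taken for harm, or a low count could be taken as reassurance although nothing was collected alongside it in the control arm. The Discussion presents the pilot as groundwork for a later effectiveness trial, and the course covers grief and suicidality, so usable harms data are worth having at this stage.

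**Working it through.** No figure in the protocol needs reproducing, because the point is structural. Each possible source of adverse-event information during the 6-week randomized period is set against the two arms:

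| Source | Section | Intervention arm | Wait-list arm |
|---|---|---|---|
| Coach monitoring | Harms; Intervention | Yes, regular | None: access starts after the 6-week assessment |
| Documentation by the research team | Harms | Follows from what the coach finds | No separate source named |
| Advice to see the general practitioner | Harms | Given, but yields no data | Given, but yields no data |
| 6-week online survey: event or life-event item | Table 2 | None | None |
| 6-week online survey: K10 and GAD7 | Table 2 | Yes | Yes |

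The table gives three results.

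1. Negative life events and other discrete adverse events have a stated route in one arm and none in the other.
2. Symptom worsening, the other example in the Harms section, can be measured identically in both arms because K10 and GAD7 are taken at baseline and 6 weeks.
3. The Statistical analysis section compares groups on the primary and secondary measures. It mentions neither a count of participants who deteriorated nor an analysis of adverse events.

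**Illustration of size.** Let n be the number per arm, p the true 6-week event rate (the same in both arms), and c the share of events that the coach detects. The expected number recorded is n × p × c in the intervention arm. It is 0 in the wait-list arm if no undescribed route exists.

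- n = 84/2 = 42. The total is from the Sample size section; equal allocation is assumed, since the article states no ratio.
- p is not in the documents. A range of 10% to 30% is assumed.
- c is not in the documents. Full capture (1.0) and half capture (0.5) are shown.

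| p | c = 1.0 | c = 0.5 | Wait list |
|---|---|---|---|
| 10% | 42 × 0.10 = 4.2 | 2.1 | 0 |
| 20% | 42 × 0.20 = 8.4 | 4.2 | 0 |
| 30% | 42 × 0.30 = 12.6 | 6.3 | 0 |

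Lower detection shrinks the intervention count but does not remove the imbalance. The illustration shows only the direction and rough scale of the artefact; it is not a prediction for this trial.

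**The case against.** The strongest reply has four parts.

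- **Another route may exist.** The Harms section never says that the coach is the sole source, and this is a condensed article. That is fair as far as it goes: exclusivity is an inference from finding no other route in the document. But the section is not silent. It fixes who monitors and when, and the method it fixes is tied to one arm. That is a stated method, not an omitted detail.
- **No comparison is promised.** The aims are feasibility and initial effects, and the Harms section describes safety handling for individual participants. This stands. The counts mislead only if someone sets them side by side, and the protocol does not say that anyone will.
- **Harms can be compared in part.** A reader might infer that no harm of any kind can be compared between arms. The documents do not support that, because both arms complete K10 and GAD7 at both times. The gap concerns discrete events, chiefly negative life events.
- **The safety statement is prospective.** A reader might infer that the protocol intends to conclude safety from these counts. It does not: its description of the intervention as safe is a judgement made beforehand to justify the level of monitoring.

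One might also suppose that monitoring reaches mainly active users. Caregivers in the focus groups preferred free choice of modules, so this is plausible, but the Harms section speaks of regular monitoring and does not tie it to use. It remains conjecture.

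**Conclusion.** The point holds in a limited form. As the protocol is written, ascertainment of adverse events depends on the arm during the whole randomized period, so events as collected give no valid between-arm comparison, and the coach's counts mix contact with risk. Under the assumptions shown (42 per arm, a common rate of 10% to 30%, half to full capture), the artefact would be about 2 to 13 recorded events against none.

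This rests on there being no undescribed route for the wait-list arm. It does not touch the primary analysis or the feasibility conclusions, and the trial is a small pilot of an intervention judged to be low risk. The point is a cheap improvement to the harms data, not a flaw that threatens the trial's main results.

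**What to change.** 1. **Same questions in both arms.** Add two or three identical items on adverse events and negative life events since baseline to the existing 6-week online assessment, and base any between-arm comparison of events on these alone.
2. **K10 deterioration by arm.** From data already collected, report the number whose K10 score rose, and the number who moved from below to above the cutoff of 20. For the second count, use as denominator those below the cutoff at baseline. Randomization is stratified at that cutoff, so these denominators should be similar in the two arms.
3. **Coach-noted events apart.** Report them separately, labelled as uncontrolled observations in the intervention arm, and not as one column of a two-arm comparison.

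These changes concern data collection and reporting only. The arrangements for acting on an event stay as they are.

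The cost is slight extra burden on respondents, one table, and a formal amendment, which the Ethical approval section requires for any modification. Recruitment began in September 2015, so anyone already assessed at 6 weeks will lack the new items, and non-responders at 6 weeks will lack them too. The K10 table covers everyone with both assessments, whenever they were enrolled.

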### Ethical approval

This study is being conducted in accordance with local laws and regulations and follows the Medical Research Guidelines for Good Clinical Practice and European Union directives to ensure trial integrity as well as participants’ safety and well-being [31]. Respondents who are interested in taking part receive detailed information about the study and have the opportunity to ask questions. Digital informed consent will be obtained from all study subjects before the start of the study. Participants are allowed to terminate study participation at any time without giving a reason. The study has been reviewed and approved by the ethics committee of VU Amsterdam, Amsterdam, the Netherlands (VCWE-2015-126). Modifications to the protocol require a formal amendment to the protocol. This will be completed by the principal investigator. All changes and amendments to the protocol are supervised and approved by the sponsor.

## Discussion

To our knowledge, this study will be the first pilot RCT to evaluate the feasibility and initial effects of E-care 4 caregivers, an online self-management intervention for nonprofessional caregivers of patients with depression. Previous research among nonprofessional caregivers in general revealed an urgent need for support [5], and group interventions showed positive results in reducing stress and experienced burden [9, 10].

The strength of the study design is the inclusion of a qualitative analysis to assess the feasibility of the intervention. Further, this pilot study will provide a reliable indication of the sample size needed for an RCT testing the effectiveness of the intervention. Only preliminary conclusions on the effectiveness of the intervention can be drawn, owing to the small sample size. Conclusions regarding the prevention of disorders is, at this stage, preliminary. Also, this intervention targets the general population, and it is possible that potential improvement cannot yet be detected. However, the population is still at higher risk for psychological complaints [4–8], so a first indication would therefore be needed.

This intervention is one of the first [16] to be developed for this type of nonprofessional caregiver, and recruitment results as well as previous research underscore the need for more support in this particular group [5]. Also, the intervention has the potential to be cost-effective [14] and relatively easy to implement in general health care to reduce costs and increase availability for professional mental health care.

This study will provide insight into the feasibility and initial effects of an online self-management intervention for nonprofessional caregivers of patients with depression. E-care 4 caregivers could potentially benefit nonprofessional caregivers, as well as patients and professionals indirectly.

### Trial status

The trial started recruitment in September 2015.

## Abbreviations

CBT: cognitive behavioral therapy
CONSORT: Consolidated Standards of Reporting Trials
GAD7: 7-item Generalized Anxiety Disorder Scale
K10: Kessler Psychological Distress Scale
RCT: randomized controlled trial
SUS: System Usability Scale
WLC: wait list control group
ZBI-12: 12-item Zarit Burden Interview
